### Experimental set-up/intervention

The experimental design includes two physical tasks (1. Physical Performance Task and 2. Precision Task) in four randomized conditions (with and without exoskeleton and with and without prior physical fatigue; *cf.*
Figures 1, 2):

Physical Performance Task (PILE task) at shoulder height:Participants will perform the Physical Performance Task at shoulder height, both with and without the exoskeleton. This task aimed to assess the impact of the exoskeleton on physical performance under normal working conditions.

Precision Task (nailing following the Fitts paradigm) at overhead height:The Precision Task involves overhead nailing activities following the Fitts paradigm (43, 44) (three predefined templates into which the nails must be precisely inserted.), simulating tasks requiring precision and skill. Participants will execute this task with and without the exoskeleton, allowing the evaluation of the exoskeleton’s influence on tasks demanding fine motor skills.

Randomization will be done by the online program www.randomizer.org.

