### Participant timeline

The study will be conducted over two separate days to mitigate potential carryover effects and ensure the avoidance of additional fatigue symptoms. On each day, participants will undergo the assigned conditions for both tasks in a randomized order, minimizing the impact of confounding variables. The sequence of conditions will be counterbalanced across participants to control for order effects.

First, the participants are welcomed and informed in writing and verbally about the aim and conduct of the study. This is followed by the recording of the anthropometric data and personal data. Then the preparations for the surface electromyography begin, including the application of the electrodes and the pre-tests (MVC). The suit for the Xsens sensors is then applied and a calibration is carried out. Finally, the sensor and the calibration for the fNIRS are carried out.

The first session then begins, depending on which task was selected first for the person. The person is then either fitted with the exoskeleton and begins the first task (Physical Performance Task or Precision Task) or performs this without the exoskeleton. If the fatigue protocol is already planned for the person at the beginning based on the randomization, this is carried out without the exoskeleton before the start of the task.

After completion of the first task, an individual break is taken before the second task begins. After completing both tasks, the person is asked to complete the questionnaires.

Due to the activity of overhead work, which already involves increased exertion because of the non-ergonomic posture, and the additional activity of screwing, physical fatigue may increase. Therefore, physical exertion is subjectively documented via the Borg scale (49) after each test session. Additionally, test sessions are spread over 2 days.

Individual breaks will be provided between each test session due to possible mental and physical exertion during the tests (Figure 3).

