### Sample size

The sample size was calculated on the outcome of muscle activity using G*power (*a priori*, ANOVA with repeated measures and interaction effect) with 2 groups (male/female), 2 tasks (Physical Performance Task, Precision Task), 2 conditions (with/without exoskeleton), and 2 fatigue protocols (with/without fatigue protocol) estimating an effect size of 0.25, an alpha error rate of 0.05 and a statistical power of 0.80, resulting in *N* = 36 participants for each group. With an estimated drop of 20% we will include a total of *N* = 80 (40 female/40 male) healthy participants with male and female participants equally.

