### Data monitoring

The whole author group will be involved into the data monitoring hosting meetings once a month. Following the data collection, the raw data will be reviewed, and possible elimination of poor data will be made (cleaning of the data set). Standardized procedures will be applied to the sEMG data sets, the fNIRS data set, and the questionnaires.

The raw data of the 3D motion analysis will be extracted, processed, and evaluated via MATLAB (Matlab R2019b, Massachusetts, USA).

The video recordings are reviewed to ensure that all measuring instruments are synchronized.

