### Statistical analysis

All data will be processed via SPSS 29.0 and evaluated using suitable statistical procedures at the significance level *α* = 0.05. These statistical procedures depend on concrete questions and include variance analyses as well as descriptive procedures.

For the analysis of the movement data (Xsens), repeated measures ANOVA will be carried out with regard to upper body flexion, lateral flexion and rotation with a comparison between the different scenarios. Furthermore, we will conduct Bonferroni *post-hoc* tests for between-subject analysis regarding differences between (1) using an exoskeleton, and (2) fatigue protocol. In addition, an SPM analysis will provide information on the sections of the activity in which a change over time can be detected.

For the analysis of muscular activation, an ANOVA with repeated measures is also used for the comparisons between the scenarios, as well as Bonferroni *post-hoc* tests for between-subject comparison. In addition, a Statistical Parameter Mapping (SPM) analysis can also be carried out here, which illustrates the deviations over time.

The subject-specific muscle synergies will be classified through k-means clustering using the Hartigan-Wong algorithm independently for each group and condition. For statistical analysis of muscle weights between groups two-way analysis of variance (ANOVAs) will be carried out, which in case of statistical significance will be followed by post-hoc comparisons through pairwise t-tests with Benjamini-Hochberg adjusted *p*-values. For all muscle weightings that show significant differences, effect sizes (Cohen’s d) will be calculated. Furthermore, the activation patterns will be analyzed through the calculation of center of activity, as well as the full width at half maximum (FWHM). Additional discretes for analysis can be number of synergies per subject and percentage of unclassifiable synergies.

All objective data recordings will be synchronized via LSL and processed with specific MATLAB pipelines.

For the analysis of the cognitive data (fNIRS), as well as the subjective perceived exertion via the Borg scale, an ANOVA with repeated measures is carried out in each case.

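### Repeated-measures ANOVA excludes, outcome by outcome, every participant with a missing run; a mixed model on all available runs would keep them

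*Protocol article*

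**What the plan says.** The Statistical analysis section of the protocol article sets the software ("All data will be processed via SPSS 29.0 and evaluated using suitable statistical procedures at the significance level") and then the method for each outcome. For Xsens data, "repeated measures ANOVA will be carried out with regard to upper body flexion, lateral flexion and rotation". For muscle activation, "an ANOVA with repeated measures is also used for the comparisons between the scenarios". For fNIRS and the Borg scale, "an ANOVA with repeated measures is carried out in each case". The section names no mixed model and no day, period or sequence term. Muscle weights from the synergy analysis are handled by a two-way ANOVA and lie outside this point.

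Each participant performs two tasks "in four randomized conditions (with and without exoskeleton and with and without prior physical fatigue" (Experimental set-up/intervention), spread over two days. On order, the Participant timeline section says "The sequence of conditions will be counterbalanced across participants to control for order effects".

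The article foresees three ways in which runs can be lost:

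- Sample size: "With an estimated drop of 20% we will include a total of" 80, from a requirement of 36 per group.
- Harms: the study is terminated for a participant with strong exhaustion or discomfort, and may be repeated on another day.
- Data monitoring: after collection, "possible elimination of poor data will be made (cleaning of the data set".

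**The concern.** Classical repeated-measures ANOVA needs a value in every within-person cell. A participant who lacks one cell is left out of that outcome's model, and the runs that were recorded for that outcome are not used. With four cells per task, or eight if both tasks enter one model, a small rate of lost runs becomes a much larger rate of lost participants.

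What is at stake is mainly precision. The margin is thin: a 20% drop from 80 leaves 64, already below the 72 that the Sample size section requires, before any recording is rejected. A second issue is the assumption about missing data. A complete-case analysis generally needs a stronger assumption than a likelihood-based model that uses every observed run. A third, smaller issue is that order is balanced by design but does not appear among the named model terms, and missing runs can break that balance.

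**Working it through.** **1. The protocol's own figures.** 2 × 36 = 72 required; 80 recruited. 80 × (1 − 0.20) = 64, and 72/80 = 0.90, so 80 recruits yield 72 only at a 10% loss. The 36 per group could not be reproduced from the stated interaction test. With effect size f = 0.25, alpha 0.05, power 0.80, two groups, eight measurements and an assumed within-person correlation of 0.5, that test needs 16 in total (10 to 30 for correlations from 0.7 to 0). The between-group test at the same settings needs 74 and has power 0.797 at 72. That is a separate matter; 72 serves here only as the protocol's target and 64 as what its own drop leaves.

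**2. Cells per participant.** Exoskeleton (2) × fatigue (2) = 4 per task; × 2 tasks = 8. The article prints neither count and does not say whether the tasks are pooled in the analysis, so both are shown.

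**3. Share of participants complete.** If each run is lost independently with probability p, the share with all m cells is (1 − p)^m. The article states no p; the values are assumptions.

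| p | 4 cells | of 72 | of 64 | 8 cells | of 72 | of 64 |
|---|---|---|---|---|---|---|
| 2% | 0.922 | 66 | 59 | 0.851 | 61 | 54 |
| 3% | 0.885 | 64 | 57 | 0.784 | 56 | 50 |
| 5% | 0.815 | 59 | 52 | 0.663 | 48 | 42 |

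The proportion of runs still available to a mixed model is 98%, 97% and 95%.

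**4. What a mixed model retains.** Take 80 participants and an eight-cell model. Each has a 20% chance of losing four runs picked at random (a stand-in for a missed second day), plus independent loss p. Assume compound symmetry with correlation 0.5 and loss unrelated to outcome, with 200 simulated patterns per setting. Information is expressed as the equivalent number of complete participants.

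| p | Complete cases | Mixed model: exoskeleton contrast | Mixed model: participant mean |
|---|---|---|---|
| 0 | 64 | 71 | 78 |
| 2% | 54 | 69 | 78 |
| 5% | 42 | 67 | 78 |

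**5. Power.** For the gender main effect, λ = f²Nm/(1 + (m − 1)ρ). At N = 64: 0.0625 × 64 × 8/(1 + 7 × 0.5) = 32/4.5 = 7.11 on 1 and 62 df, giving power 0.75. For the three rows above, complete-case power is 0.75, 0.67 and 0.56, against about 0.83 in each with all runs. The gender-by-exoskeleton interaction is less exposed. Treated as two groups by two levels with f = 0.25 and correlation 0.5, it needs 34 in total (power 0.807), so even 42 complete participants would suffice on that reading.

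**6. Leaving out day.** For a day shift of b within-person standard deviations, with conditions differing between days, within-person variance rises by the factor 1 + b²/4. For assumed b = 0.2, 0.5 and 0.8 this is 1.01, 1.06 and 1.16.

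**The case against.** The article condenses a fuller plan, and model terms and missing-data rules are commonly left to a document not shown here. That stands for the day and period terms, which would not be a finding alone. It does not stand for the method, which the article fixes for four groups of outcomes. The article does not name the SPSS procedure; if a mixed model was meant, one sentence saying so would settle the matter.

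Several points on size also stand:

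- No rejection rate is given, and independence is assumed. Poor recordings that cluster in a few people would cost fewer participants.
- A nailing run has three templates and a PILE run has repeated cycles, so a bad segment need not empty a cell.
- Terminated sessions may be repeated, which could restore runs.
- The article does not say how much of the 20% drop is partial, or whether it already covers unusable recordings.

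Three stronger readings are tempting and not supported:

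- A reader might infer that one bad recording removes all of a person's data. The outcomes are analysed separately, so a rejected EMG recording leaves that person's fNIRS, Xsens and Borg analyses untouched.
- A reader might infer that the gender contrast is biased. The Discussion expects more discomfort in women and the Harms section links termination to discomfort, so this is plausible. But nothing in the article shows that loss will follow that pattern, and a mixed model would not cure loss that depends on unobserved values.
- A reader might infer that the missing order terms invalidate the crossover. With counterbalanced order and complete data, the omission mainly adds residual variance.

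**Conclusion.** The point holds, and the plan should be changed. The stated method discards observed runs in a design where the protocol itself foresees incomplete data, and a better method is available in the same software.

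At an assumed independent loss of 2% to 5% of runs, 8% to 19% of participants drop out of an outcome's model if tasks are analysed separately, and 15% to 34% if they are pooled. The four-cell figures are the fair minimum, because the article does not commit to pooling. The fall in power to 0.56 is for the gender main effect only. It rests on the pooled model, the 20% partial dropout, a 5% run loss and a correlation of 0.5, none of which the article states in that form.

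The gain is precision from partly observed participants, and validity under missing at random. Participants who leave before any run add nothing under either method. Day and period terms are a secondary reason for the same change: they remove residual variance and protect the comparison once missing runs break the counterbalancing.

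**What to change.** For the movement, muscle activation, fNIRS and Borg outcomes, make the primary analysis of each a linear mixed model (SPSS MIXED) on all available runs. Include fixed effects for gender, exoskeleton, fatigue and their interactions, fitted per task or with task as a further factor, plus fixed day and period (run order) and a random participant effect. State the covariance structure in advance. Keep the complete-case repeated-measures ANOVA as a sensitivity analysis, and report for each outcome how many participants and runs enter each analysis.

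The cost is a change of analysis wording, a little more modelling work and one covariance choice. Software, data collection and design stay as they are.

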## Discussion

The aim of this study is to increase the understanding of the effects of exoskeleton use, especially with regard to cross-gender comparisons while exploring cognitive and physical workload within real-world scenarios. The main research question will address the gender differences effects of using an upper body exoskeleton in the dual task working situations regarding muscle synergies, upper body posture, cognitive resources, comfort, discomfort and usability. Moreover, an additional focus will lay on the effects of a physical fatigue protocol on the proposed outcomes.

The randomized crossover study design (*cf.*
Figures 1, 2) ensures a balanced distribution of order effects and the high number of participants that will be included in the study is unique according to the combined and comprehensive methods (muscle synergy concept and fNIRS).

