### Cognitive-motor interference

Next, to the movement aspects, the use of exoskeletons involves a complex interplay between users and the support system, encompassing psychological and physical elements in human-machine interaction (HMI) or cognitive-motor interference. This interaction is often observed in scenarios requiring the concurrent execution of tasks, involving cognitive and/or motor resources and leading to cognitive-motor interference [CMI; (35)]. CMI, characterized by performance decline in dual-task situations, may incur dual-task costs (36). Various models, rooted in the principles that performance quality is tied to processing activity quantity, and this processing is inherently limited, provide insights into the concept of CMI (37). Initial studies have delved into cognitive load associated with exoskeleton use across various contexts, unveiling CMI effects that impact pace and reaction times [e.g., (38)]. Evidence indicates that exoskeleton use requires heightened effort in terms of motor adaptation and neurocognitive control. Factors such as cognitive load, cognitive-motor process complexity, demographic variables, and exoskeleton characteristics contribute to CMI. Recent reviews corroborate the impact of upper-limb exoskeletons on cognitive workload and physical performance. In a study by Taygi et al. (33), neurophysiological adaptations during exoskeleton use were investigated. Their research uncovered variations in neural activity and functional connectivity within the primary motor cortex, offering valuable insights into the influence of exoskeletons on the nervous system. In the realm of exoskeleton research, a meticulous exploration of the discomfort aspect has yielded valuable insights from several studies. For example, Otten et al. (9) presented noteworthy findings, revealing a tangible decrease in overall task effort with the implementation of the Lucy exoskeleton. This reduction suggests a potential ergonomic advantage associated with exoskeleton use.

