### Gender differences

With respect to the research questions, we hypothesize that potential gender differences will be observed within the muscle synergies. We think that the exoskeleton use will reduce shoulder muscle activity significantly [e.g., (54)] but first studies suggest that women might have less muscle activation in the shoulder muscles while wearing an exoskeleton (33). On the other hand, with respect to the design and the weight of the exoskeleton, women potentially could use different movement patterns to manage the tasks (56) due to differences in biomechanical and anthropometric trunk muscle geometry of females and males (56, 57). We anticipate that women show more bending backwards movements including a higher compensatory muscle activation in the abdominal and neck muscles. However, this idea has to be proven within our experimental design.

Moreover, as women are merely not integrated into the iterative designing processes of exoskeletons, yet, we propose more discomfort and less usability in the ratings by the women. This discomfort especially will be reported for the shoulder region (41).

In line with the cognitive resource theories (36), this discomfort might lead to more attentional resources spending on the discomfort and less resources available for the working DT situation. This will increase the cognitive-motor interference especially in the DT situation and could be observed with more cortical activation in the prefrontal cortex [*cf.* (35)]. Moreover, the working accuracy will decrease (58).

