### Fatigue effects

Regarding physical fatigue we suppose that firstly the overall gender effects might be reduced. One potential explanation lies in the idea that the additional required motor resources after fatigue will reduce the discomfort effect. According to fatigue it has to be assumed that the task management requires more muscle activity that can be reduced by the exoskeleton use (59). As this is relevant for both genders, the muscle activity and accompanying synergies might converge. Nevertheless, it is unclear if the weight of the exoskeleton affects muscle activity between men and women differently.

However, the organizing of body movement after fatigue needs more executive control in the motor cortex (60) and this will lead to less attentional resources available for the detailing recognition of the discomfort. This hypothesis will be proven by the analysis of the fNIRS data, regarding a potential shift from parietal to frontal cortex activation. This mechanism should be equal for male and female participants and might only be affected by age (61).

Moreover, as more resources for postural control and motor adjustments will be required after fatigue, the cognitive-motor interference in the DT condition will rise while movement accuracy will decrease. If the exoskeleton use will reduce this effect, it needs to be examined within our experimental design. On the other hand, the physical fatigue could also increase the proposed differences in upper body postures (more bending backwards of the women). This hypothesis would lead to increased muscle activity in the supporting muscles and might change muscle synergy patterns.

In summary, the knowledge of this study will contribute to refining and optimally implementing exoskeletons, with a focus on reducing fatigue and mitigating musculoskeletal risks, while considering the nuances of movement variability and cognitive resource allocation.

Furthermore, we would like to emphasize that the study also highlights the challenges, such as user discomfort and frustration, which can hinder the widespread adoption of this technology in real-world scenarios, especially for females.

The innovative focus lies on task and gender-specific variability including the muscle synergy approach. Analyzing muscle synergies can provide a nuanced understanding of muscle coordination and function, as well as the effects of interventions such as fatigue protocols or wearing an exoskeleton on these interactions.

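### The Discussion states dual-task interference hypotheses, but the design has no dual-task condition, so a dual-task cost cannot be estimated; exoskeleton and fatigue effects can

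*Protocol article*

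**What the plan says.** **Hypotheses.** The Discussion opens by placing the main research question in the setting of "using an upper body exoskeleton in the dual task working situations". Under Gender differences, discomfort in women is expected to draw on attention: "This will increase the cognitive-motor interference especially in the DT situation". That section adds that the effect could show as more prefrontal activation and that accuracy will fall. Under Fatigue effects the prediction is that "the cognitive-motor interference in the DT condition will rise while movement accuracy will decrease".

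**Definition.** The Introduction, under Cognitive-motor interference, says: "CMI, characterized by performance decline in dual-task situations, may incur dual-task costs".

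**Design.** Experimental set-up/intervention says "The experimental design includes two physical tasks" and runs them "in four randomized conditions (with and without exoskeleton and with and without prior physical fatigue". The Sample size section lists the same factors plus gender. Participant timeline has the second task start after the first is finished and a break has been taken. The last paragraph under Fatigue effects gives added cognitive tasks as an example of what this design cannot address.

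**Formal questions.** The list at the end of the Introduction asks about gender effects of exoskeleton use in both tasks, with and without prior fatigue, on cognitive resources among other outcomes. It does not mention dual-tasking.

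**Analysis.** Statistical analysis gives a repeated-measures ANOVA "For the analysis of the cognitive data (fNIRS), as well as the subjective perceived exertion via the Borg scale". Nailing time and errors are recorded (Precision task; Speed accuracy trade offs), and the Abstract says motor performance will be analysed.

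**The concern.** The hypotheses refer to a condition that the Methods never create. Interference, as the article uses the term, is a loss of performance when two demands compete. Showing it needs performance under dual and under single demands, and only the second kind of cell exists.

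What is at stake is the interpretation of the cognitive results. The Introduction allows two opposite pathways: physical support may free cognitive resources, or managing the device may use them up. With no dual-task contrast, an fNIRS difference in either direction could be given a resource explanation after the fact, and nothing in the design could contradict it.

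**Working it through.** The article gives no figure on this point, so the check compares the contrast that the hypotheses need with those that the design supplies.

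**1. Contrast needed.** From the Introduction's definition, for performance outcome Y:

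dual-task cost = Y(dual task) - Y(single task)

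The Gender differences hypothesis needs the female-minus-male difference in this cost. The Fatigue effects hypothesis needs its change after fatigue.

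**2. Cells available.** From Experimental set-up/intervention and Sample size:

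- tasks: 2 (Physical Performance, Precision)
- exoskeleton: 2 (with, without)
- prior fatigue: 2 (with, without)
- cells per participant: 2 x 2 x 2 = 8
- cells with a concurrent secondary task: 0

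The two tasks cannot act as each other's reference. They are done in sequence, and they differ in movement, working height and load. With no Y(dual task) cell, the cost is undefined for every participant, so a larger sample does not help.

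**3. What the design can estimate.** For each person, task and fatigue state:

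exoskeleton effect = Y(with) - Y(without)

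This gives 2 tasks x 2 fatigue states = 4 differences per person. Comparing them between women and men gives gender x exoskeleton. Comparing that across fatigue states gives gender x exoskeleton x fatigue. These contrasts exist for fNIRS and, in the Precision Task, for nailing time and errors. They are what questions 1c and 2c ask for.

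**4. Why fNIRS alone is not enough.** The Gender differences section expects the exoskeleton to reduce shoulder muscle activity. The with-minus-without contrast therefore changes physical load as well as any attentional demand of the device:

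observed fNIRS change = part due to attentional demand + part due to physical load

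One observed quantity cannot separate the two parts. A rise in prefrontal activation fits interference but does not establish it.

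**5. Behavioural evidence on hand.** Time and errors are noted for each of three templates, with and without the exoskeleton. They can show whether performance falls when activation rises. They do not turn the contrast into a dual-task cost, since the device could also slow or disturb the movement mechanically.

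**The case against.** The strongest reply is that wearing the exoskeleton is itself the second demand, with the no-exoskeleton condition as reference. The Abstract says the device may introduce interference. The Introduction allows competing demands to be motor as well as cognitive, and says the device may have to be integrated into automatized movement. This stands as support for an exoskeleton-related workload effect. It does not rescue the DT hypotheses: Fatigue effects names a DT condition and then asks separately whether the exoskeleton reduces the effect seen there. The device cannot be both the second task and the possible remedy for its cost.

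A second reply is that the Discussion wording is loose, that the formal questions avoid it, and that the authors call their expected outcomes speculative and concede limits on what the design can say about cognitive resources. All of this is so, and it limits the point to the Discussion. But the Discussion uses the phrase for the main research question and derives directional predictions from it.

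A third reply is that no passage commits the authors to reporting an fNIRS difference as interference. That is fair. The Gender differences section does, however, name prefrontal activation as the way interference could be observed.

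A reader might also infer that task performance will go untested. The documents do not support that. The Abstract says motor performance will be analysed, and Statistical analysis has a general sentence on variance analyses. The outcome-by-outcome text merely names no test for time or errors, a detail that an article may leave to a fuller plan.

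**Conclusion.** The point holds for the dual-task claims in the Discussion. None of the 8 within-person cells is a dual-task cell, so the cost, its gender difference and its change with fatigue are not estimable. An fNIRS result alone cannot fill the gap.

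It would go too far to infer that the cognitive questions cannot be answered. Questions 1c and 2c, and the section Brain hemodynamics using fNIRS, already ask about exoskeleton and fatigue effects, which the design estimates in every participant who completes the conditions. They need no restating. The synergy, posture and comfort comparisons are also unaffected.

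The conclusion assumes that the Methods text describes every condition and that no concurrent task appears only in the study-flow figures, which were not available for this check. The authors' own remark on added cognitive tasks makes such a task unlikely. The change is worth making because it decides what may be concluded from the fNIRS data.

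**What to change.** 1. Remove the DT wording and the dual-task interference claims from the opening of the Discussion, Gender differences and Fatigue effects.
2. Align those hypotheses with the formal questions: gender x exoskeleton, and gender x exoskeleton x fatigue, effects on cortical activation and on task performance.
3. In Statistical analysis, name the within-person with-minus-without change in nailing time and in error rate as the performance contrast, to be read beside the fNIRS result.
4. State that a rise in activation together with a fall in performance will be described as an exoskeleton-related cost, not a dual-task cost.

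The cost is a narrower claim, some rewording and one more model on data already being recorded. No participants or sessions are added. If the authors want to keep the dual-task claims, they must describe a concurrent task and a single-task reference. Crossing that factor with the present design would take the cells per participant from 8 to 8 x 2 = 16, a far larger change.
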